### Data analysis

Data will be stored on password-protected UCL computers in locked departments and will be anonymised prior to use. Since this is a feasibility study, all analyses other than recruitment rate and dropout rates should be considered exploratory. RIPC and control groups will be compared including both baseline characteristics and secondary outcomes. Continuous variables will be presented using means and standard deviations or medians and inter-quartile ranges, as appropriate, and binary variables will be presented as frequency counts and percentages. The mean difference in proportions (for binary outcomes) and the mean or median difference (for continuous outcomes) between the two groups will be explored and presented with 95 % confidence intervals.

This important data will be used to help the design of the multi-centre RCT.

Results will be analysed via Statistical Package for Social Sciences (SPSS) (IBM Chicago, IL, USA).

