### Power calculation

A power calculation is not required for a pilot feasibility study [19]. However, guidance would suggest that 50 patients would be suitable for a feasibility study [20] with 25 randomized to receive RIPC and 25 to liver transplantation as per standard.

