### Randomization

Participants are randomized to either the control or intervention group following induction of anaesthesia and collection of baseline blood samples. Randomization is performed via a random number sealed envelope system. Both the surgeon and the patient will be blinded to whether the patient receives RIPC.

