### Trial protocol

Induction and maintenance of anaesthesia will be performed by intravenous propofol. The use of volatile inhaled induction agents such as sevoflurane have been shown to exert a degree of pharmacological preconditioning [21, 22] and as such they will be avoided.

Following induction but before the intervention, baseline blood and urine samples will be collected for measurement of pre-operative circulating cytokine levels and markers of renal parenchymal injury in both the blood and the urine.

A layer of stockinette will be applied to the left upper thigh with a wide pneumatic tourniquet applied over it in accordance with safe and recommended practices by the Association of Peri-operative Registered Nurses (AORN) [23] and Royal Free Hospital (RFH) departmental guidelines.

In those undergoing RIPC, the tourniquet will be inflated to 200 mmHg for 5 min followed by 5 min of reperfusion. This will be repeated three times.

In the control group, a sham will consist of the pneumatic tourniquet being placed on the left upper thigh without being inflated. The transplant will then proceed as standard.

Further blood samples will be collected 2 h following reperfusion of the graft to measure circulating cytokine levels post reperfusion. At the same time, two post reperfusion biopsies will be obtained. One of these biopsies will be fixed in 10 % natural buffered formalin for 48 h before being embedded in paraffin for H&E staining. IR injury will be graded by a pathologist according to the Suzuki classification of liver IR injury [24]. The second biopsy will be processed to extract fresh intra-hepatic lymphocytes for analysis by flow cytometry.

A further blood and urine sample will be obtained 24 h post reperfusion to measure circulating cytokine levels and markers of renal parenchymal injury both in the blood and urine.

All patients will receive standard post-operative care.

Routine clinical data will be collected including local complications as a result of RIPC, liver biochemistry, clotting profiles, urea and creatinine levels, post-operative complications, requirements for organ support, length of stay in the intensive care department and total hospital stay. Patients will be followed up for 3 months. A flow diagram of the trial is included in Fig. 1.

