### Outcome measures

The aim of this study is to assess the feasibility of recruiting liver transplant recipients and performing RIPC immediately prior to liver transplantations. The primary and secondary outcomes (Table 2) will help design a subsequent multi-centre RCT of RIPC in liver transplant recipients.

**Table 2 Tab2:** Primary and secondary endpoints

Primary endpoints	Ability to recruit patients to the trial
	Feasibility of performing RIPC in liver transplant recipients
	Safety of RIPC in liver transplant recipients
Secondary endpoints	AST levels on the third post-operative day [30]
	Incidence of acute kidney injury and need for renal replacement therapy
	Length of stay in intensive care and total hospital stay
	Incidence of vascular thrombotic events
	Incidence of biliary complications
	Incidence of post-operative infections
	Incidence of acute rejection in the first months post transplantation
	Circulating cytokine levels 2 h post reperfusion of the liver graft
	T cell accumulation and activation in the liver 2 h post reperfusion
	Urinary and serum NGAL levels 2 h post reperfusion

The criteria to progress to a full trial will be determined based on a consent rate of at least 60 % and post randomization dropout rate from the study of less than 30 %.

The safety of RIPC will be measured by incidence of localized complications following RIPC to include the development of a deep vein thrombosis or pulmonary embolus, the development of localized cellulitis and pain or paresthesia of the left lower limb following RIPC.

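### The stated comparison of post-reperfusion cytokines makes no use of the pre-randomization values: valid, but it may give up precision that is already paid for

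*Protocol article*

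**What the plan says.** The Trial protocol section states: "Following induction but before the intervention, baseline blood and urine samples will be collected for measurement of pre-operative circulating cytokine levels". The same sentence covers markers of renal injury in blood and urine. The Randomization section places allocation after the baseline blood draw: "Participants are randomized to either the control or intervention group following induction of anaesthesia and collection of baseline blood samples".

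Table 2 (Outcome measures) lists two matching secondary endpoints: "Circulating cytokine levels 2 h post reperfusion of the liver graft" and "Urinary and serum NGAL levels 2 h post reperfusion". Cytokines are sampled again at 24 h: "A further blood and urine sample will be obtained 24 h post reperfusion to measure circulating cytokine levels and markers of renal parenchymal injury".

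The Data analysis section gives a single method for continuous outcomes: "the mean or median difference (for continuous outcomes) between the two groups will be explored and presented with 95 % confidence intervals". Its only stated use of baseline data is a comparison of baseline characteristics between the groups. It labels everything except recruitment and dropout rates as exploratory. The Discussion nevertheless says that the preliminary efficacy data will help to set the endpoints and power of the multi-centre trial.

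**The concern.** A cytokine level taken before allocation cannot have been affected by it, so it is a legitimate covariate for the level after reperfusion. A two-group mean or median difference, in its natural reading, leaves that covariate out. If patients with high levels before surgery also tend to have high levels afterwards, between-patient variation that could be removed stays in the standard error.

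What is at stake is precision in data meant for planning. A wider interval tells the designers of the main trial less about which mechanistic outcomes are promising. A plain difference also does not supply the residual variance or the baseline-outcome correlation, which are needed to size a main trial analysed with adjustment.

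**Working it through.** The plan has no figure to reproduce: the Power calculation section makes no calculation and takes its sample size from guidance ("50 patients would be suitable for a feasibility study [20] with 25 randomized to receive RIPC and 25 to liver transplantation as per standard"). The check is therefore how much a baseline-adjusted interval differs from the stated one at that size.

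**Inputs**
- 25 patients per arm, N = 50 (Power calculation section).
- 95 % two-sided interval (Data analysis section).
- Correlation r between the pre-intervention and post-reperfusion value: not in the documents. It is an assumption, varied from 0 to 0.7.
- All results are in units of the outcome SD. They assume complete data, equal variances and a linear relation, and they concern a difference in means (on the log scale if values are skewed). They do not carry over directly to a median difference.

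**Plain difference**

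SE = √(1/25 + 1/25) = √0.08 = 0.283. Half-width = t(48) × SE = 2.011 × 0.283 = 0.569.

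**Baseline-adjusted difference**

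The residual variance is (1 − r²). Estimating the slope in a small sample inflates the variance on average by (N − 3)/(N − 4) = 47/46, and one degree of freedom is lost:

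Half-width = t(47) × 0.283 × √[(1 − r²) × 47/46].

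For r = 0.5: 0.75 × 47/46 = 0.766; √0.766 = 0.875; 2.012 × 0.283 × 0.875 = 0.498.

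| r (assumed) | Variance factor | Half-width | Ratio to 0.569 (from unrounded values) | Interval | Unadjusted N with equal precision (50 / variance factor) |
|---|---|---|---|---|---|
| 0 | 1.022 | 0.575 | 1.011 | 1 % wider | 49 |
| 0.2 | 0.981 | 0.564 | 0.991 | 1 % narrower | 51 |
| 0.3 | 0.930 | 0.549 | 0.965 | 3.5 % narrower | 54 |
| 0.5 | 0.766 | 0.498 | 0.876 | 12 % narrower | 65 |
| 0.7 | 0.521 | 0.411 | 0.722 | 28 % narrower | 96 |

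The two methods break even at r of about 0.15.

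**Chance imbalance**

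The difference in baseline means between arms also has SE 0.283 SD. The probability that it exceeds 0.25 SD in either direction is 0.38. Given the sample drawn, the plain difference is shifted by r times the imbalance. At an imbalance of one SE the shift is 0.3 × 0.283 = 0.08, 0.5 × 0.283 = 0.14 or 0.7 × 0.283 = 0.20 SD. This is another view of the same variance, not an addition to it: over repeated randomizations the shifts average to zero and the plain interval already allows for them.

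**Which outcomes qualify**
- Cytokines: measured before randomization, at 2 h and at 24 h. Only 2 h is a Table 2 endpoint.
- NGAL: Table 2 sets it at 2 h, but the Trial protocol section describes renal-marker samples only at baseline and 24 h. That section does not name NGAL; that it is one of the baseline markers is an inference from the Discussion.
- Intra-hepatic T cells: no pre-intervention biopsy is described.
- Day-3 AST: no baseline value is specified for this comparison.

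**The case against.** The strongest objection is that this reads a decision into silence. The Data analysis section neither says that the differences are unadjusted nor excludes covariates, and an ANCOVA estimate is itself a mean difference with an interval. A journal article condenses the plan, and a covariate model could stand in an analysis plan that is not shown. Part of this holds: a reader might infer that the plan rules out adjustment, and the text does not say so. But the section does fix a contrast and an interval for all continuous outcomes, and a median difference reads naturally as a two-group comparison with no baseline term. Proposing a better contrast from data already collected goes beyond asking for missing detail.

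Second, the gain may be nil. The baseline precedes surgery and the outcome follows reperfusion of a new graft, which the Discussion describes as setting off a large systemic cytokine response. A low correlation is plausible, and the documents do not settle it. This stands, and it is why the size is given as a range that includes a small loss.

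Third, a reader might infer that ignoring the baseline biases the result or invalidates the interval. It does not: under randomization the plain difference is unbiased and its interval is valid.

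Fourth, nothing decisive rests on these outcomes. The progression criteria are a consent rate of at least 60 % and dropout below 30 %, and the primary endpoints are recruitment, feasibility and safety. This stands and keeps the severity low.

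**Conclusion.** The point holds for cytokines as a low-severity matter of efficiency. The stated analysis is sound, but for an outcome with a pre-randomization measurement an adjusted estimate is the better choice. The downside is about 1 % of interval width if the correlation is zero; the gain is about 12 % at 0.5 and 28 % at 0.7. These figures rest on assumed correlations, 25 complete patients per arm and a linear relation.

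The NGAL part cannot be acted on yet, because Table 2 and the Trial protocol section disagree on when renal markers are sampled. A reader might also extend the point to the key secondary outcome, day-3 AST, or to the biopsy outcomes. The documents describe no corresponding baseline for either, so the point does not reach them. The feasibility and safety conclusions are unaffected.

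**What to change.** In the Data analysis section, state that:

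- cytokine levels at 2 h and 24 h are each analysed by ANCOVA on arm and the pre-intervention value of the same cytokine, on the log scale if skewed, with a stated rule for values below the detection limit;
- the adjusted difference (or ratio of geometric means, if logged) is reported with its 95 % interval, and the plain difference is kept as descriptive;
- the baseline-outcome correlation and residual variance are reported for planning the main trial.

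Before applying the same model to NGAL, reconcile the 2 h endpoint in Table 2 with the sampling times in the Trial protocol section, and confirm that NGAL is among the baseline markers.

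For cytokines the cost is a few sentences of text and one degree of freedom. No further samples or patients are needed, and SPSS, the package named in the article, fits the model.

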### Dissemination

It is anticipated that the results of the study will be presented at the British Transplant Society annual meeting and reported in a peer-reviewed journal of interest to the transplant community.

We will publish a research report on the University College London’s website and the Royal Free NHS trusts’ website.

## Discussion

IR injury is a major cause of graft loss, morbidity and mortality following liver transplantation [1, 25]. Due to the increase utilization of grafts from extended criteria donors which are more prone to IR injury [2], strategies to ameliorate IR injury are a key research goal. We have previously shown that RIPC reduces hepatic IR injury in small animal models [13, 14, 26]. Previous trials have investigated IPC of donor livers prior to retrieval [5–8] but failed to discern any clinical benefit. IR injury is not confined to the liver but results in a systemic cytokine storm, immune activation and multi-organ dysfunction. In successful small animal models, preconditioning is performed in the same individual as the reperfusion injury occurs and therefore the process of performing RIPC in the recipient may be more efficacious at reducing the systemic inflammatory response associated with IR injury reducing graft injury and end organ damage.

Several different protocols for RIPC exist, and there is no current consensus as to which protocol is best. Three cycles of 5 min of ischaemia have been shown to ameliorate IR injury in small animal models [27] and in patients undergoing coronary artery bypass graft surgery [28], and as such we have elected to use this preconditioning protocol in this trial.

This is the first trial to investigate whether recipient RIPC can improve the outcome of human liver transplant recipients. As such, we have chosen to perform a pilot feasibility study of 50 patients initially. We have designed this pilot study as a blinded randomized control trial to give us the strongest pilot data to adequately power and design the main trial. The data from this initial patient cohort will allow us to determine patient recruitment, support of the liver transplant physicians and surgeons, the feasibility of carrying out the period of preconditioning between anaesthesia and commencing surgery, the safety of limb ischaemia in liver transplant recipients and to gain preliminary data on efficacy with which to determine the endpoints and power required for a subsequent multi-centre RCT.

We have chosen to exclude patients with a history of venous thrombo-embolic disease, peripheral arterial disease and localized limb infections to minimize risk to participating patients during a yet unproven intervention. We have also chosen to exclude patients undergoing liver transplantation for acute liver failure, on the super-urgent list, as a transplantation in this setting is associated with a threefold increased risk of morbidity and mortality [29]. In a small trial, this would introduce significant bias to the results. Furthermore, these patients have altered levels of consciousness due to encephalopathy and consent is a problem for their inclusion in this feasibility study. Patients undergoing simultaneous liver kidney transplantation have been excluded to remove the bias of the added surgical stress and the inclusion of patients with severe pre-operative renal impairment who are offered combined transplants.

We have chosen AST on the third post-operative day as an important endpoint as recent work has shown that this correlates strongly with overall graft function, post-operative mortality, need for organ support and incidence of post-operative infective complications [30]. With current 90-day graft loss rates of 3.5 % and 90-day mortality rates of 6.9 % following elective liver transplant in the UK [29], a very large RCT would be required to determine significant benefit following RIPC based on these endpoints which is currently unfeasible. We have also chosen to measure urinary and serum neutrophil gelatinase-associated lipocalin (NGAL) levels as a sensitive marker [31] of evidence of acute kidney injury (AKI) post transplantation as this is a common complication post liver transplantation, and reduction in the incidence of end organ damage would provide a further hard endpoint to be used as an outcome in the future RCT in combination with day 3 AST levels.

Evidence of a reduction in IR injury and the associated systemic inflammatory response will be measured by analysing the extent of IR injury and immune cell activation in post reperfusion biopsies and circulating serum cytokines.

In summary, this is the first trial to investigate RIPC in the setting of liver transplantation. RIPC has been shown to ameliorate IR injury in renal transplantation [15, 17]. Samples from this trial will be analysed to provide evidence of a reduction in immune activation by RIPC.

If successful, this inexpensive holistic intervention could improve outcome following liver transplantation and allow the implantation of more grafts from extended criteria donors—widening the donor pool.

## Abbreviations

AKI: acute kidney injury
AORN: Association of Peri-operative Registered Nurses
AST: aspartate transferase
DCD: donor after cardiac death
IPC: ischaemic preconditioning
IR: ischaemia reperfusion
mmHg: millimetres of mercury
OLT: orthotopic liver transplantation
RCT: randomized controlled trial
RFH: Royal Free Hospital
RIP: remote ischaemic preconditioning
